# COMplex Fracture Orthopedic Rehabilitation (COMFORT) - Real-time visual biofeedback on weight bearing versus standard training methods in the treatment of proximal femur fractures in the elderly: study protocol for a multicenter randomized controlled trial

**DOI:** 10.1186/s13063-018-2612-9

**Published:** 2018-04-12

**Keywords:** Proximal femur fracture, Weight-bearing, Biofeedback, Gait analysis, SensiStep, Fracture rehabilitation

## Abstract

**Background:**

Proximal femur fractures are a common injury after low energy trauma in the elderly. Most rehabilitation programs are based on restoring mobility and early resumption of weight-bearing. However, therapy compliance is low in patients following lower extremity fractures. Moreover, little is known about the relevance of gait parameters and how to steer the rehabilitation after proximal femur fractures in the elderly. Therefore, the aim of this prospective, randomized controlled trial is to gain insight in gait parameters and evaluate if real-time visual biofeedback can improve therapy compliance after proximal femur fractures in the elderly.

**Methods:**

This is a two-arm, parallel-design, prospective, randomized controlled trial. Inclusion criteria are age ≥ 60 years, a proximal femur fracture following low energy trauma, and unrestricted-weight bearing. Exclusion criteria are cognitive impairment and limited mobility before trauma. Participants are randomized into either the control group, which receives care as usual, or the intervention group, which receives real-time visual biofeedback about weight-bearing during gait in addition to care as usual. Spatiotemporal gait parameters will be measured in 94 participants per group during a 30-m walk with an ambulatory biofeedback system (SensiStep). The progress of rehabilitation will be evaluated by the primary outcome parameters maximum peak load and step duration in relation to the discharge date. Secondary outcome parameters include other spatiotemporal gait parameters in relation to discharge date. Furthermore, the gait parameters will be related to three validated clinical tests: Elderly Mobility Scale; Functional Ambulation Categories; and Visual Analogue Scale. The primary hypothesis is that participants in the intervention group will show improved and faster rehabilitation compared to the control group.

**Discussion:**

The first aim of this multicenter trial is to investigate the normal gait patterns after proximal femur fractures in the elderly. The use of biofeedback systems during rehabilitation after proximal femur fractures in the elderly is promising; therefore, the second aim is to investigate the effect of real-time visual biofeedback on gait after proximal femur fractures in the elderly. This could lead to improved outcome. In addition, analysis of the population may indicate characteristics of subgroups that benefit from feedback, making a differentiated approach in rehabilitation strategy possible.

**Trial registration:**

TrialRegister.nl, NTR6794. Registered on 31 October 2017.

**Electronic supplementary material:**

The online version of this article (10.1186/s13063-018-2612-9) contains supplementary material, which is available to authorized users.

## Background

Due to the ageing population, the worldwide incidence of hip fractures will rise from 1.66 million in 1990 to 6.26 million by 2050 [1]. Hip fractures have a high mortality and high morbidity [2]. Loss of function is common after a hip fracture and patients experience difficulties in their return to society or to their previous habitat. This leads to long-term care in rehabilitation facilities, which is the largest component in the total costs in the treatment of hip fracture patients [3].

Most rehabilitation programs are based on restoration of mobility and early resumption of weight-bearing [4]. Weight-bearing is important as it helps to maintain muscle and bone mass [5]. In addition, early weight-bearing could also lead to improved fracture healing through mechanotransduction [6]. Therefore, early (partial) weight-bearing is generally advocated and trained with walking aids under supervision of a physical therapist. Bathroom scales are commonly used to guide the amount of weight-bearing to the patient. This method is not only unreliable, but also not very helpful for patients as information about the amount of weight-bearing is only provided in the static situation and lost in the dynamic situation.

Although the bathroom scale is still the gold standard in most rehabilitation clinics, the introduction of biofeedback systems is promising as information can be provided in the dynamic situation [7]. Previous studies have already shown improvement in partial and full weight-bearing when biofeedback systems were used, compared to standard training methods [8, 9]. For example, visual biofeedback has shown positive results in the treatment after Parkinsons’s disease, in the late period after stroke, and after cerebral palsy [10–12]. Also, auditory and visual biofeedback have shown significant improvements in weight-bearing after lower extremity fractures [9, 13, 14]. Although these results seem promising, the effect of real-time visual biofeedback on weight-bearing during rehabilitation after proximal femur fractures in the elderly is still unknown.

Therefore, in this randomized controlled trial (RCT), real-time visual biofeedback will be provided to the patient and healthcare professional in the clinical setting by the ambulatory biofeedback system SensiStep (Evalan BV, Amsterdam, The Netherlands). This biofeedback system was previously validated in static and dynamic situations [15]. In short, the system consists of an in-sole force sensor, which is able to measure weight-bearing reliably and continuously during gait. Generated peak loads are directly translated into a LED signal, to provide real-time feedback to the patient. The same signal is sent to a tablet, resulting in a real-time graphical illustration of each step shown to the healthcare professional. By using this biofeedback system, patients can be guided to the optimal level of weight-bearing. This potentially leads to better functional outcome, as well as improved fracture healing through mechanotransduction.

In this RCT, it will be investigated whether elderly patients recover faster or better after proximal femur fractures if they receive real-time visual biofeedback in the clinical setting. The control group receives care as usual and the intervention group receives care as usual with the addition of real-time visual biofeedback to improve weight-bearing to the optimal level. Hypothetically, patients in the intervention group show: (1) an increase in maximum peak loads; and (2) faster step durations at an earlier timepoint in their rehabilitation. Furthermore, patients in the intervention group recover faster, which results in an earlier discharge date.

## Methods

### Study design

This protocol is described according to the SPIRIT (Standard Protocol Items: Recommendations for Interventional Trials) Statement (see Additional file 1). The study is an international, multicenter trial conducted between March 2017 and August 2018 in the Netherlands and Sweden. Rehabilitation centers focused on geriatric rehabilitation are asked to participate in this study. In order to ensure the quality and expertise of the participating centers, a minimum inclusion rate of at least 20 patients per year is expected. Therefore, the number of eligible patients is screened in each center before their participation in the study. Measurements will be performed by trained physical therapists at the site and all physical therapists are experienced in geriatric trauma care. Before the start of the study, all physical therapists agreed on the study treatment regime during multiple consensus meetings and were trained to uniformly implement this study treatment. Participating geriatric rehabilitation clinics are listed in Table 1.

**Table 1 Tab1:** Participating rehabilitation clinics

Clinic	Place	Allocation (group)
Zorgspectrum *Geinsche Hof* *[name]* *[name]*	Nieuwegein (NL)	Intervention
Warande *Bovenwegen* *[name]* *[name]*	Zeist (NL)	Intervention
Warande *Diakonessenhuis* *[name]* *[name]*	Zeist (NL)	Intervention
Beweging 3.0 *Meander Medical Center* *[name]* *[name]*	Amersfoort (NL)	Control
Evean *[name]* *[name]*	Amsterdam / Zaandam (NL)	Intervention
Beweging 3.0 *Woonzorgcentrum De Pol* *[name]* *[name]*	Nijkerk (NL)	Control
Cordaan *In het Zomerpark* *[name]* *[name]*	Nieuw-Vennep (NL)	Control
azM Herstelzorg *[name]* *[name]*	Maastricht (NL)	Control
Zorggroep Groningen *[name]* *[name]*	Groningen (NL)	Intervention
Careyn *Nieuw Tamarinde* *[name]* *[name]*	Utrecht (NL)	Control
Telge Rehab *[name]* *[name]*	Södertälje (SE)	Control

Participating geriatric rehabilitation clinics in The Netherlands and Sweden. Clinics were allocated to either the control or the intervention group

This trial is a two-arm, parallel-design, prospective RCT. Based on a previous pilot study, the average length of rehabilitation is 44 days, with a standard deviation of 17. Using a power of 0.80, an alpha of 5%, and an expected reduction of seven days (one week) in two-sided testing, a sample size of 94 participants per group was calculated. Participants will be allocated to either the control group or the intervention group using a stratified cluster randomization according to the sealed opaque envelope principle. First, all rehabilitation clinics were divided into two groups depending on the inclusion rate: < 2 vs. ≥ 2 eligible participants per month. This division was made to avoid skewing of inclusion rate in both arms. Then in both groups, clinics were randomized by the principal investigator into the control or intervention group using the sealed opaque envelope principle. This resulted in six rehabilitation clinics in the control group and five rehabilitation clinics in the intervention group (Table 1). Randomization per center, or cluster randomization, was chosen for two reasons. First, individual selection bias by the physical therapist is minimized. Second, and more importantly, the physical therapists and participants within one center can now provide a single treatment, either care as usual or care as usual, with real-time visual biofeedback. Considering the constant interaction between physical therapists, as well as between participants, individual randomization would increase the risk of data collection errors.

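### The 94 per group is sized for individually randomised patients, but 11 whole clinics were randomised, so the stated 80% power does not belong to this design

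*Protocol article*

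**What the plan says.** The sample-size paragraph under Methods, Study design, rests on length of rehabilitation. From a pilot study, "the average length of rehabilitation is 44 days, with a standard deviation of 17". With power 0.80 and alpha 5%, it gives the target and the result together: "an expected reduction of seven days (one week) in two-sided testing, a sample size of 94 participants per group was calculated".

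The same paragraph then says that allocation was made "using a stratified cluster randomization according to the sealed opaque envelope principle", with clinics stratified by accrual rate. Six clinics went to control and five to intervention, and Table 1 lists them by arm. The article defends the choice openly: "Randomization per center, or cluster randomization, was chosen for two reasons". It states no ICC, design effect or calculation of the number of clinics.

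Two other places bear on the point. Outcome measures says that a multidisciplinary team sets the discharge date under the institution's normal practice. The abstract describes allocation differently: "Participants are randomized into either the control group, which receives care as usual, or the intervention group".

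**The concern.** A sample size for independent patients holds under clinic randomisation only if patients in one clinic are no more alike than patients in different clinics. That is hard to assume here. The powered outcome is length of stay, and its end is decided under each clinic's own discharge practice. Each clinic also follows its own physiotherapy protocol (Methods, Protocol), and the clinics lie in two countries.

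If stays correlate within clinic, the trial has less than its stated 80% power for a 7-day reduction. The 80% is the only power figure in the article. A reader who trusts it could take a non-significant result as evidence against a one-week benefit when the design had limited ability to show one. The abstract's wording makes this more likely, because it does not reveal that clinics were the unit of allocation.

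**Working it through.** **Inputs from the article (Study design):** SD 17 days; difference 7 days; two-sided alpha 0.05; power 0.80; 94 per group; 5 intervention and 6 control clinics. **Assumed:** the ICC, which the article does not give, and equal clinic sizes within each arm.

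**1. Reproduce the stated figure.** For independent patients, n per group = 2 × (1.960 + 0.842)² × 17² / 7² = 92.6, so 93 with the normal formula. The two-sample t-test needs 93.55, so 94. At 94 per group its power is 0.802, and at 93 it is 0.798. The article's 94 is therefore the individual-randomisation answer with no inflation.

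**2. Cluster sizes.** 188 / 11 = 17.1 patients per clinic overall; 94 / 5 = 18.8 in the intervention arm and 94 / 6 = 15.7 in the control arm.

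**3. Standard error under clinic randomisation.** The design effect (DE) in each arm is 1 + (m − 1) × ICC, and SE = 17 × √(DE_int/94 + DE_con/94). For example, at ICC 0.02, DE_int = 1 + 17.8 × 0.02 = 1.356 and DE_con = 1 + 14.67 × 0.02 = 1.293, so SE = 17 × √(2.649/94) = 2.854 days.

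**4. Power and detectable difference.** Normal reference: power = Φ(7/SE − 1.960), and the difference detectable with 80% power is 2.80 × SE. Reference with 11 − 2 = 9 degrees of freedom: power comes from the noncentral t, and the detectable difference is 3.15 × SE.

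| ICC (assumed) | SE, days | Power, normal | Power, 9 df | Detectable days, normal | Detectable days, 9 df |
|---|---|---|---|---|---|
| 0 | 2.480 | 0.806 | 0.710 | 6.9 | 7.8 |
| 0.005 | 2.578 | 0.775 | 0.677 | 7.2 | 8.1 |
| 0.01 | 2.673 | 0.745 | 0.646 | 7.5 | 8.4 |
| 0.02 | 2.854 | 0.689 | 0.590 | 8.0 | 9.0 |
| 0.05 | 3.338 | 0.555 | 0.465 | 9.4 | 10.5 |
| 0.10 | 4.016 | 0.414 | 0.344 | 11.3 | 12.6 |

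**5. How much slack there is.** Even with the normal reference, 94 exceeds the required 92.58 by a factor of only 1.0153. The mean of (m − 1) over the two arms is (17.8 + 14.67)/2 = 16.2, so the slack is used up at ICC = 0.0153/16.2, about 0.001. For practical purposes, any ICC above 0 takes power below 80%.

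**The case against.** **The ICC is unknown, so the shortfall is too.** This stands for size but not for direction. At ICC 0.005 or 0.01 the normal-reference loss is modest (0.775 and 0.745). A reader might infer that power is certainly far below 80%. The article does not support that, and only the direction is secure.

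**The 9 degrees of freedom are a reviewer's choice.** This also stands. The Statistical analysis section names multiple regression and no clinic-level test, and how clinic enters the model may be set out in an analysis plan that is not shown. A clinic-level test that also allowed for the accrual strata would have 8 degrees of freedom (power 0.70 at ICC 0). Covariate adjustment could recover some power, and unequal clinic sizes would cost some. Both references are therefore shown. The point does not depend on the 9-df column, because the normal column is below 80% throughout the assumed range.

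**A stronger claim is tempting: that at ICC 0.05 no number of patients in 11 clinics could detect 7 days.** The limiting SE is 17 × √(0.05 × (1/5 + 1/6)) = 2.30 days. With 9 df the floor is 2.30 × 3.15, about 7.2 days, but with the normal reference it is 2.30 × 2.80, about 6.4 days, which is below 7. The claim depends on the reference chosen and is not made here. Nor is 11 necessarily final: Monitoring lists the need for further centres among the items to be discussed at the interim looks.

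**The cluster design is disclosed.** It is, in Study design and Table 1. The abstract's sentence makes no power claim; it is a related labelling fault and not a second sample-size error. The registry entry is not at hand, so nothing is said about it.

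**An analysis plan could deal with this.** It could change the analysis. It cannot turn 94 per group, derived in the article from fully stated inputs without inflation, into an 80%-power size for 11 randomised clinics with correlated outcomes.

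**Conclusion.** The concern holds as a mismatch between design and sample size. A reader might call it an arithmetic slip, but the arithmetic is right for the design it assumes and reproduces exactly. It is the wrong design for this trial.

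The stated 80% is not the power of the trial as described. Over an assumed ICC of 0.01 to 0.10, power for 7 days runs from 0.745 down to 0.414 with a normal reference, and from 0.646 down to 0.344 on 9 df. The detectable difference runs from 7.5 to 11.3 days, or from 8.4 to 12.6 days. These figures assume 94 patients per arm, 5 against 6 clinics, equal clinic sizes within each arm, a total SD of 17 days, and no gain from covariates.

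A reader might also infer that any non-significant result will fail to exclude a 7-day reduction. That cannot be said in advance, because it depends on the confidence interval obtained.

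**What to change.** - **Study design:** keep the planned patients. Replace the 80% statement with the power and detectable difference for the actual design (5 against 6 clinics, about 17 patients each) over a stated ICC range, and name the degrees of freedom. Take the range from the pilot or the two-month pre-trial registration of eligible patients if either holds length of stay by clinic; otherwise say that it is assumed. Update the figures if centres are added.
- **Abstract:** say that clinics, not participants, were randomised.
- **Interpretation:** state that a non-significant result will be read by whether its clinic-adjusted confidence interval includes a 7-day reduction.

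The cost is rewording and a less favourable stated power. No extra patients are required.

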### Statistical analysis

Statistical analysis on outcome measures will be conducted using Statistical Package for the Social Sciences (SPSS). First, data distribution will be assessed. Second, missing data will be handled by a multiple imputation technique. The primary analysis will be based on an intention-to-treat principle. Also, a per-protocol analysis will be performed as sensitivity analysis to assess the robustness of the results to protocol deviations [17]. The primary goal is to find a relation between the gait parameters (maximum peak load and step duration) and the discharge date. In addition, other spatiotemporal gait parameters measured by the SensiStep will be analyzed for this relation as well. The secondary goal is to find a relation between the gait parameters and the clinical measurements (i.e. EMS, FAC, and VAS). Relations between all data will be examined using multiple regression analysis.

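### Clinics were randomised within two inclusion-rate strata, but the stated regression names neither clinic nor stratum; once clinic is allowed for, the stratum should be in the model too (minor)

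*Protocol article*

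**What the plan says.** Under Methods, Study design, the clinics were first split by volume: "First, all rehabilitation clinics were divided into two groups depending on the inclusion rate: < 2 vs. ≥ 2 eligible participants per month". The purpose given is logistical: "This division was made to avoid skewing of inclusion rate in both arms". Allocation followed inside each group: "Then in both groups, clinics were randomized by the principal investigator into the control or intervention group". The outcome was six control and five intervention clinics. The article does not say how many of each fall in each stratum.

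The same section takes its planning figures from a pilot study ("the average length of rehabilitation is 44 days, with a standard deviation of 17") and sizes the trial from them: "Using a power of 0.80, an alpha of 5%, and an expected reduction of seven days (one week) in two-sided testing", from which "a sample size of 94 participants per group was calculated".

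Under Methods, Statistical analysis, the model is given in one sentence: "Relations between all data will be examined using multiple regression analysis". No covariates are listed, and neither the clinic nor the inclusion-rate group is mentioned.

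**The concern.** Two features of the randomisation should carry into any comparison of the arms: the unit (clinic) and the restriction (two strata). The stated analysis mentions neither, and the two omissions act in opposite directions.

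Ignoring clinic treats patients as independent when whole clinics were allocated, so standard errors are too small. Ignoring the stratum works the other way in an analysis that does respect clinics. Near-balance on stratum keeps most of the between-stratum difference out of the true variance of the arm contrast. A model without the stratum leaves that difference in the between-clinic residual, so the estimated standard error is too large. A clinic random effect with no stratum term has the same weakness.

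With 11 randomised units, the clinic-level variance already limits the trial, so a needless inflation of it matters. An odd number of clinics also means that one stratum cannot be split equally between arms, so an unadjusted contrast can be slightly off if the strata differ.

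**Working it through.** **1. The plan's own figure.** With SD 17, difference 7, two-sided alpha 0.05 and power 0.80, n per group = 2(1.960 + 0.842)² × 17² / 7² = 92.6, so 93 by the normal approximation. The exact noncentral t gives power 0.7976 at 93 and 0.8019 at 94. The stated 94 is reproduced. It is the formula for individually randomised patients, with no clinic or stratum term.

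**2. Assumptions, because the article gives no figures.** Strata of 5 low-volume and 6 high-volume clinics; 11 and 22 patients per clinic (5 × 11 + 6 × 22 = 187, against 188 planned); intervention in 2 of 5 and 3 of 6; ICC 0.05, with 0.01 and 0.10 as a range; gap in mean stay between strata of 0, 3.5 or 7 days. Total variance is 17² = 289.

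**3. Patient-level regression, no clinic term.** The arms hold 2 × 11 + 3 × 22 = 88 and 3 × 11 + 3 × 22 = 99 patients.
- Nominal SE = 17 × √(1/88 + 1/99) = 2.49 days.
- True variance at ICC 0.05 = 14.45 × [(2 × 11² + 3 × 22²)/88² + (3 × 11² + 3 × 22²)/99²] + 274.55 × (1/88 + 1/99) = 14.45 × (0.2188 + 0.1852) + 5.89 = 11.73, so the true SE is 3.42 days.
- The same sum gives a true SE of 2.70 at ICC 0.01 and 4.15 at ICC 0.10.
- Simulated type I error is about 7%, 15% and 24% at ICC 0.01, 0.05 and 0.10.
- For a 7-day gap at ICC 0.05, adding the stratum moves the model SE only from 2.52 to 2.48, and type I error stays near 15%.

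**4. Clinic-level analysis (t-test on clinic means), ICC 0.05.** The variance of a clinic mean is 14.45 + 274.55/m: 39.41 for m = 11 and 26.93 for m = 22.
- True SE of the unadjusted contrast = √[(2 × 39.41 + 3 × 26.93)/5² + (3 × 39.41 + 3 × 26.93)/6²] = √(6.38 + 5.53) = 3.45 days. With the stratum term it is 3.47.
- Expected within-arm sum of squares from noise = (4/5) × 159.61 + (5/6) × 199.02 = 293.5. A gap g adds g² × (2 × 3/5 + 3 × 3/6) = 2.7g².
- Estimated SE without the stratum = √[(293.5 + 2.7g²)/9 × (1/5 + 1/6)]: 3.46 for g = 0, 3.65 for g = 3.5 and 4.17 for g = 7. The last is a root mean square; the mean simulated SE is 4.05.
- The high-volume share is 3/5 in intervention and 3/6 in control, so the unadjusted contrast shifts by 0.1g, which is 0.7 days for g = 7.

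**5. Simulated power for a 7-day effect in that clinic-level analysis (9 v 8 df), ICC 0.05.**

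| Stratum gap | Without stratum | With stratum |
|---|---|---|
| 0 | 44% | 43% |
| 3.5 days, high-volume clinics longer | 37% | 43% |
| 7 days, high-volume clinics longer | 25% | 44% |
| 7 days, low-volume clinics longer | 34% | 41% |

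Repeat runs move these by one or two points; a longer run gave 24% v 43% and 36% v 43% for the last two rows. Unadjusted type I error at a 7-day gap is about 2.5%. For a 3.5-day gap with low-volume clinics longer, there is no gain (44% v 43.5%). For a 7-day gap with high-volume clinics longer, power is about 30% v 59% at ICC 0.01 and 20% v 33% at ICC 0.10.

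**The case against.** The strongest objection is that silence is not a decision. The Statistical analysis section lists no covariates of any kind, and a journal article may leave them to a full protocol or SAP that is not shown. That stands so far as it goes: the article does not rule the stratum out, and the point closes if the full documents already contain both terms. But these are not optional covariates. The article itself sets out the unit and the strata of randomisation, then states a model that is connected to neither.

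Second, a reader might infer that the stated regression is conservative, with intervals too wide. The article does not support that. Read as written, with no clinic term, the model errs the other way, and the stratum term alone leaves it there. The conservative direction belongs only to an analysis that already respects clinics. The power figures therefore describe a refinement of such an analysis, not of the regression in the article.

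Third, nothing in the article links clinic volume to stay or gait. The strata were made to balance recruitment. The expected minimum of 20 patients a year is 20/12 = 1.67 a month, so if it is met the low stratum spans only about 1.67 to 2. A 7-day gap equals the whole planned effect and should be read as the top of the range. This stands, and it is why the point is minor. Part of the largest loss also comes from the assumed arm imbalance within strata, and it shrinks when the gap is reversed.

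**Conclusion.** The point holds as a minor one. The randomisation is by clinic within two strata, and the only stated model names neither. The larger fault is the missing clinic term, which makes standard errors too narrow for any ICC above roughly 0.01 in these scenarios. Correcting that brings the stratum into play. In a clinic-level analysis, omitting it costs nothing if volume is unrelated to outcome, between nothing and about 6 points of power at a 3.5-day gap, and about 7 to 19 points at a 7-day gap, depending on its direction. These sizes rest on an assumed ICC of 0.05, assumed clinic and stratum sizes, an assumed split of arms within strata, and a volume-outcome link that the article does not document. The inflated standard error and the low type I error do not depend on the direction of the gap; the power loss does.

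**What to change.** In every between-arm model, include a clinic-level error term (or analyse clinic means) together with the randomisation stratum (< 2 v ≥ 2 eligible participants per month) as a fixed effect. Specify the two together, because the stratum term alone does not correct the standard errors. If a permutation test is used for the 11 clinics, restrict it to re-allocations within strata. If the full protocol or SAP already does this, a sentence saying so is enough.

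The stratum is known for every clinic, so no new data are needed. Adding it takes clinic-level degrees of freedom from 9 to 8, which costs about 1 point of power if volume is unrelated to outcome (44% to 43% above). Allowing for clinic has its own, larger effect on power: the 43 to 44% above compares with the planned 80%. That belongs to the clustering problem, not to the stratum term.
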